### **Vital Signs**

Supine blood pressure and heart rate (absolute values and change from baseline) will be summarized by treatment groups and scheduled visit.

**ECG**

The incidence of patients with a clinically significant abnormal ECG result will be provided.

A summary of shifts in 12-lead ECG abnormalities from baseline will be performed by scheduled visits.

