### 3.2.2. Exclusion criteria

To be eligible for enrolment in the study, patients must NOT meet any of the following criteria:

1. Presence of a mixed *Plasmodium* infection.
2. Presence of other clinical condition requiring hospitalization.
3. Presence of significant anaemia, as defined by  $\text{Hb} < 8 \text{ g/dL}$ .
4. Known history or evidence of clinically significant disorders such as cardiovascular (including arrhythmia, QTc interval greater than or equal to 450 msec), respiratory (including active tuberculosis), hepatic, renal, gastrointestinal, immunological (including active HIV-AIDS), neurological (including auditory), endocrine, infectious, malignancy, psychiatric or other abnormality (including recent head trauma).
5. Known history of hypersensitivity, allergic or adverse reactions to pyronaridine, chloroquine or artesunate or other artemisinins.
6. Known history of hypersensitivity, allergic or adverse reactions to chloroquine, primaquine and related agents.
7. Known active Hepatitis A IgM (HAV-IgM), Hepatitis B surface antigen (HBsAg) or Hepatitis C antibody (HCV Ab).
8. Known seropositive HIV antibody.
9. Have received any antimalarial treatment in the preceding 2 weeks, as determined by history and, whenever feasible, by screening test.
10. Have received antibacterial with known antimalarial activity in the preceding 2 weeks.

11. Have received any investigational drug within the past 4 weeks.
12. Liver function tests (AST/ALT levels) more than 2.5 times the upper limit of normal range.
13. Known significant renal impairment as indicated by serum creatinine levels of more than 1.4 mg/dL.
14. Female patients of child-bearing potential must be neither pregnant (as demonstrated by a negative pregnancy test) nor lactating, and must be willing to take measures to not become pregnant during the study period.
15. Previous participation in the present clinical trial with pyronaridine artesunate.

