### **5.2.3. ECG**

The incidence and nature of clinically significant ECG abnormalities will be assessed.

A 12-lead resting ECG will be performed at screening on Day 0 (Pre-Dose), and approximately 2 - 4 hours after study drug administration on Day 2, as well as on Day 28. Further ECG measurements at other times may be taken as clinically indicated.

Clinical indications for further ECG recordings would be the finding of obvious abnormalities of rhythm, and/or obvious changes from the previous ECG or if the patient experiences cardiac-type symptoms such as chest pain, palpitation or shortness of breath. If the ECG recording device provides an automated report then this can be used as a guide as to whether a further ECG would be required. The automated report should not, however, be the only source of information as to whether an abnormality is present for reporting purposes.

For each ECG recording, care must be taken to ensure that the leads are placed in the same place at each time point. Only one recording is required, however, after the recording has been made, on each occasion the ECG should be inspected to ensure that it is of sufficient quality for interpretation (i.e. all of the leads are in their correct place and there is minimum artefact). If the quality is not adequate the recording should be repeated. Once this has been performed a copy should be made from the original recording. One copy of the ECG should be included with the CRF and the other with the source documents.

The ECG recording should be read and interpreted by the Investigator. Should changes from baseline be present, the Investigator should assess whether these are clinically significant and if so record the findings on the CRF and if considered a detrimental change, record as an adverse event. A proportion of ECGs from

each site will be sent to a central blinded reviewer for review. A report on the central review will be sent back to site.

The ECG should be reviewed for:

1. Waveforms P, QRS and T as well as the presence of U waves
2. Rhythm (abnormal rhythms as well as tachycardia and bradycardia)
3. Evidence of abnormalities of PR, QT, and ST segments
4. An assessment of overall “normality” of the ECG and where borderline or abnormal whether the abnormality is clinically significant
5. Any change from baseline or from one ECG to the next

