**Safety endpoints:**

- Incidence of any adverse events or clinically significant laboratory abnormalities
- Vital signs, new physical examination abnormalities
- ECG abnormalities

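### ECG safety is summarised only as investigator-judged categories, with no post-dose QTc value named for recording or analysis

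*Protocol*

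**What the plan says.** Comparing safety with chloroquine is part of the primary objective (Section 2), and Section 9.5.1 lists "ECG abnormalities" among the safety endpoints. The ECG paragraph of Section 9.5.2 then gives two outputs: "The incidence of patients with a clinically significant abnormal ECG result will be provided", and "A summary of shifts in 12-lead ECG abnormalities from baseline will be performed by scheduled visits".

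The categories come from Section 5.2.3: "The ECG recording should be read and interpreted by the Investigator". The review list there includes "An assessment of overall “normality” of the ECG and where borderline or abnormal whether the abnormality is clinically significant". Only a proportion of tracings goes to a blinded central reader, whose report returns to the site. A copy of each tracing goes with the CRF, but the section names no interval in msec to be recorded after dosing.

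Elsewhere the protocol treats comparable data as numbers:
- Exclusion criterion 4 (Section 3.2.2) covers a "QTc interval greater than or equal to 450 msec".
- Laboratory data in Section 9.5.2 get an incidence table and a shift table, as ECGs do, and summary statistics as well.
- Blood pressure and heart rate get both the level and the change since baseline, by arm and visit.

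The scheduled ECGs are at screening, on Day 2 about 2 to 4 hours after dosing, and on Day 28.

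**The concern.** QTc is a measured interval, and the protocol relies on it as a number to decide eligibility. After dosing, the planned analysis keeps only whether an investigator called the tracing abnormal or clinically significant. Eligible patients start below 450 msec, so a modest systematic shift would leave many of them in the same category and would show only weakly in either table.

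The Day 2 tracing, 2 to 4 hours after the third dose, falls within the pyronaridine Tmax range of 1.6 to 4.8 hours given in the Phase I summary of Section 1. It is therefore the scheduled recording best placed to carry information about a drug effect. The plan names no quantitative use for it. What is at stake is how much the trial can say about QTc on pyronaridine artesunate compared with chloroquine, within a safety comparison that is part of its primary objective.

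**Working it through.** **The plan's own figure.** The only stated sample size is for Day 14 cure (Section 9.4): 90% cure in both arms, a margin of 10 points, two-sided 95% interval, 90% power, 205 evaluable per arm. The Farrington-Manning method gives 204.3, which rounds up to 205. Allowing for 10% drop-out, 410 / 0.9 = 455.6, so 456. The figure reproduces. The protocol states no power or precision for ECG data.

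**Inputs for the QTc check.** From the protocol: 205 per arm. Assumed, and not in the protocol: SD of QTc change 15 to 30 msec, normal distributions, a true difference d of 5, 7.5 or 10 msec, a two-sided 5% level, and a cut that a proportion p0 = 1%, 5% or 10% of comparator patients exceed. The single cut stands in for an abnormality call.

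**Formulas.**
- Continuous: SE = SD × √(2/205); power = Φ(d/SE − 1.96).
- Categorical: p1 = P(Z > z(p0) − d/SD), where z(p0) is the standard normal value exceeded with probability p0; then a two-proportion z-test of p1 against p0.

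**Worked case, SD 20, d = 5, p0 = 5%.** SE = 20 × √(2/205) = 1.975; 5/1.975 = 2.53; power = Φ(0.57) = 72%. On the cut, p1 = P(Z > 1.645 − 0.25) = 8.15%. Comparing 8.15% with 5% at 205 per arm has 25% power.

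| d (msec) | SD (msec) | Continuous | Cut 1% | Cut 5% | Cut 10% |
|---|---|---|---|---|---|
| 5 | 15 | 92% | 18% | 42% | 56% |
| 5 | 20 | 72% | 11% | 25% | 35% |
| 5 | 30 | 39% | 7% | 13% | 17% |
| 7.5 | 20 | 97% | 22% | 51% | 67% |
| 10 | 15 | >99% | 64% | 96% | 99% |
| 10 | 20 | >99% | 38% | 78% | 90% |

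At 5 msec the loss is about 22 to 74 points. At 10 msec with SD 15 to 20 and a cut at 5 to 10%, it shrinks to about 1 to 22 points. The 95% interval for the mean difference would have a half-width of 1.96 × SD × √(2/205), which is 2.9 msec at SD 15 and 5.8 msec at SD 30.

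**Second model, same question.** Take 228 per arm, a comparator Day 2 mean QTc of 400 to 420 msec, an SD of the Day 2 value of 20 to 25 msec, and abnormal defined as 450 msec or more (all assumed except the 228). A 5 msec difference has 10 to 31% power on the category against 57 to 76% on the mean. A 10 msec difference has 32 to 88% against 99% or more. If clinically significant ECGs are rare, separating 1% from 2% has 14% power.

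**The case against.** The strongest reply is that Section 9 calls itself a summary and defers to a detailed analysis plan. Nothing in the ECG paragraph excludes interval tables, and Section 9.1 already has continuous variables summarised descriptively. That is fair as far as it goes. But Section 9.1 can act only on values held as data, and Section 5.2.3 names no post-dose msec value to record. What is captured has to be settled in the protocol and CRF. The tracings kept with the CRF would allow later measurement, but at more cost than entering the values at the time.

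A second reply is that power is the wrong yardstick, because the ECG analysis is descriptive and no ECG test is planned. This stands, and the figures show relative information only. It also stands that the single-cut model simplifies a clinical judgement that covers rhythm and waveform as well. Section 5.2.3 does ask the investigator to note change from one ECG to the next.

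Third, the Phase II study in Section 1 reports central reading of all ECGs with no notable effects. That lowers the prior concern, but the summary reports no comparison with chloroquine.

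Three stronger readings are tempting and not supported. A reader might infer that a 5 to 10 msec difference would usually be missed; the 10 msec rows above show up to 99% power on the cut. A reader might infer that the Day 2 ECG was deliberately timed to the peak; the protocol gives no reason for 2 to 4 hours. A reader might infer that an absence of shifts would be taken as proof of similar cardiac safety; the protocol does not say so.

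**Conclusion.** The point holds as an inexpensive improvement to the analysis. The protocol fixes the ECG outputs as two judgement-based categorical tables, gives laboratory data and vital signs a continuous summary that ECGs lack, and names no post-dose interval to record. For a 5 msec difference the assumed scenarios give 39 to 92% power on the continuous scale against 7 to 56% on a cut. The gap narrows for a 10 msec shift when the SD is 15 to 20 msec and the cut is not extreme. At SD 30 msec even the continuous comparison has only 39% power for 5 msec, so it is better but not decisive. All of this rests on SDs, shifts and cut-offs that the documents do not give. The textual gap does not depend on them.

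**What to change.** In Section 5.2.3 and the CRF, record QT, heart rate or RR, and QTc (one named correction for all patients) as numeric fields for the scheduled Day 0, Day 2 and Day 28 ECGs.

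In the ECG paragraph of Section 9.5.2, add a summary by treatment group of the absolute values and their change from baseline at Days 2 and 28, with a two-sided 95% confidence interval for the between-arm difference in Day 2 QTc change. Adjustment for baseline QTc is optional. Keep the incidence and shift tables.

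No extra ECG, visit or patient is needed. The cost is some data entry and one more table. Where a site's device prints no automated report, the intervals must be measured by hand, and local readings carry measurement noise that should be acknowledged when results are reported.

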**Physical Examination**

Physical examination assessments will be summarised by visit.

**9.5.3. Interim analyses**

A blind interim analysis will be performed when 50% of the patients have reached the Day 14 timepoint to confirm the expected cure rate. The sample size may be re-assessed if the observed cure rate is lower than expected.

## **10. ETHICS**

### **10.1. Ethics Review**

The Investigator must submit to his/her local Ethics Committee the following documents: Investigator Brochure, signed protocol, informed consent and any other material relevant to the study such as advertising, in line with local regulations. The final study protocol, including the final version of the Informed Consent Form, must be approved or given a favourable opinion in writing by a local Ethics Committee. The Investigator must provide written documentation to the effect that the Ethics Committee has given favourable opinion to the protocol and informed consent. The Ethics Committee must also acknowledge having reviewed the current Investigator Brochure. Final approval must be provided to the Sponsor before any patient can be enrolled into the study. A membership list of the Ethics Committee must be provided to Sponsor before commencement of the study, using the form provided by MMV (see Attachment 10).

The principal Investigator(s) is responsible for informing the local Ethics Committee (EC) of any amendment to the protocol in accordance with local requirements. The protocol must be re-approved by the EC annually, as local regulations require.

Either the Investigator(s) or Sponsor must submit progress reports to the EC according to local regulations and guidelines. The principal Investigator(s) must also provide the EC with any reports of SAEs from the study site.

### **10.2. Ethical Conduct of the Study**

This study will be conducted in compliance with the study protocol. The patient's informed consent will be obtained according to the ethical principles stated in the Declaration of Helsinki 2000 version (amended in Tokyo 2004) (see Attachment 8), the applicable guidelines for ICH GCP, and the applicable laws and regulations of the participating countries.

### **10.3. Patient Information and Consent**

The informed consent document will be used to explain the risks and benefits of study participation to the parent or guardian of the patient in simple terms before the patient will be entered into the study. The informed consent document

contains a statement that the consent is freely given, that the parent or guardian of the patient is aware of the risks and benefits of entering the study, and that the patient is free to withdraw from the study at any time. Written consent must be given by the legal representative, after the receipt of detailed information on the study. Where appropriate, children will be asked to provide assent.

The Investigator is responsible for ensuring that informed consent is obtained from each legal representative and for obtaining the appropriate signatures and dates on the informed consent document prior to the performance of any protocol procedures and prior to the administration of study medication. A copy of the signed and dated informed consent form will be offered to the patient's parent or guardian. The signed and dated original consent form will be retained with the study records. Patients cannot undergo study-related procedures until the informed consent form has been signed and dated. Pertinent dosing information, scheduled visit dates, and instruction for contacting the Investigator will be on the study medication package or the consent form, as appropriate. The draft informed consent should be provided for review to the Sponsor prior submission to the Ethical Committee. The elements which should appear in the informed consent form are available in Attachment 9. If modifications are made according to local requirements, any new version has to be approved by Sponsor.

Given that some patients for inclusion in this study may not be capable of giving legal consent, written consent must be obtained from next of kin. In the case where the next of kin are unable to read, an impartial witness should be present during the entire informed consent discussion. After the next of kin has orally consented to participate in the study, the witness's signature on the form will attest that the information in the informed consent form and patient information sheet was accurately explained and understood. In case of a parent or guardian of the patient who cannot provide informed consent in writing, a thumbprint to indicate consent in the presence of two witnesses is acceptable. Permission from the parent or guardian must be obtained in the case of assenting minors.

The CRFs for this study will contain a section for documenting the date of patient informed consent and this must be completed appropriately. If new safety information results in significant changes in the risk/benefit assessment, the consent form and patient information sheet should be reviewed and updated if necessary. All parents or guardians of patients (including those already being treated) should be informed of the new information, given a copy of the revised

consent form and give their consent or assent to continue the study.

The principal Investigator(s) at each centre will ensure that the parent or guardian of the patient is given full and adequate oral and written information about the nature, purpose, possible risk and benefit of the study. Patients and their parent or guardian must also be notified that they are free to discontinue from the study at any time. The patient and parent or guardian should be given the opportunity to ask questions and should be allowed time to consider the information provided.

#### **10.4. Patient Data Protection**

The Informed Consent Form will explain that study data will be stored in a computer database, maintaining confidentiality in accordance with GCP. Patients in this database will be identified by initials or patient number only. The Informed Consent Form will also explain that for data verification purposes, authorised representatives of Sponsor, a regulatory authority, an EC may require direct access to parts of the hospital or practice records relevant to the study, including patient medical history.

## Attachment 2 Study Plan

|                                                                      | Treatment period  |                |                |                | Follow-up      |                |                |                |                             |                |                |
|----------------------------------------------------------------------|-------------------|----------------|----------------|----------------|----------------|----------------|----------------|----------------|-----------------------------|----------------|----------------|
|                                                                      | Day 0             | Day 0          | Day 1          | Day 2          | Day 3          | Day 7          | Day 14         | Day 21         | Day 28 or
day of failure | Day 35         | Day 42         |
|                                                                      | Screening         | Randomization  |                |                |                |                |                |                |                             |                |                |
| Informed consent                                                     | •                 |                |                |                |                |                |                |                |                             |                |                |
| Study drug administration                                            |                   | •              | •              | •              |                |                |                |                |                             |                |                |
| Primaquine administration a                               |                   |                |                |                |                |                |                |                | •                           | •              | •              |
| Demographic Data/Medical History/History of medications & procedures | •                 |                |                |                |                |                |                |                |                             |                |                |
| Physical examination                                                 | •                 |                |                |                | •              |                |                |                | •                           |                | •              |
| Body weight                                                          | •                 |                |                |                |                |                |                |                | •                           |                |                |
| Height                                                               | •                 |                |                |                |                |                |                |                |                             |                |                |
| Vital signs                                                          | •                 |                | •              | •              | •              | •              | •              | •              | •                           | •              | •              |
| Body temperature b                                        | •                 | •              | •              | •              | •              | •              | •              | •              | •                           | •              | •              |
| Clinical signs and symptoms of malaria                               | •                 |                | •              | •              | •              | • c | • c | • c | • c              | • c | • c |
| ECG (12-lead)                                                        | •                 |                |                | •              |                | • d | • d |                | •                           |                | • d |
| Haematology                                                          | •                 |                |                |                | •              | •              |                |                | •                           |                | •              |
| Blood Biochemistry /Urinalysis                                       | •                 |                |                |                | •              | •              |                |                | •                           |                | • e |
| Thick blood films                                                    | •                 | • f | • f | • f | •              | •              | •              | •              | •                           | •              | •              |
| Thin blood films                                                     | •                 |                |                |                |                | • g | • g | • g | • g              | • g | • g |
| Pyronaridine and artesunate concentration                            |                   |                | • h | • h | • h | • h | • h | • h | • h              | • h | • h |
| Molecular markers (PCR)                                              |                   | •              | •              |                |                | • i | • i | • i | • i              | • i | • i |
| G-6-PD testing                                                       | •                 |                |                |                |                |                |                |                |                             |                |                |
| Urinary test for anti-malarial drugs j                    | •                 |                |                |                |                |                |                |                |                             |                |                |
| Urine hCG pregnancy test k                                | •                 |                |                |                |                |                | •              |                | •                           |                | •              |
| AE monitoring                                                        | Record throughout |                |                |                |                |                |                |                |                             |                |                |
| Concomitant medications/Procedures                                   |                   |                |                |                |                |                |                |                |                             |                |                |

a) For patients with normal G-6-PD activity, oral primaquine treatment (once daily for 14 days) will be started on Day 28, after all assessments have been performed (including confirmation of negative pregnancy test for women of childbearing potential).

b) Every 8 hours over at least 72 hours following the first study drug administration or temperature normalisation for at least two readings 8 and 24 hours apart, then at each visit.

c) If clinically indicated and any day in case of fever.

d) If clinically indicated.

e) Should be performed only if clinically significant abnormalities are observed.

f) Thick blood films will be examined every 8 hours until at least 72 hours or until a negative smear had been recorded for at least between 8 hours and 24 hours apart, then at each visit.

g) Thin blood smear will also be taken from Day 7 whenever parasitological blood samples are taken, and reserved in the event of recrudescence, to confirm *Plasmodium* species.

h) A blood sample to measure pyronaridine levels must be taken in case of treatment failure. Furthermore, for pyronaridine population PK, 1 sample will be taken between D0 (post-dose) and D3 and another between D4 and D42. For artesunate PK, 1 sample will be taken on D0 (post-dose) or on D2 and a second one on D3.

i) PCR samples will be collected and reserved. Centralized PCR analysis will be performed at baseline and in case of re-appearing parasitaemia.

j) If feasible

k) For females of childbearing potential.

## Attachment 3

